### Sample Size and Power Calculation

Our goal is to randomize approximately 120 primary care clinicians from over 40 primary care practice sites into either the TELESCOPE intervention arm or the EUC arm. We anticipated that it would be feasible to recruit on average 3–4 patients from each of the 120 clinicians, resulting in 420 patients in total (210 patients per arm). We evaluated statistical power and effect sizes based on these assumptions for the quality of the SDM process, our primary outcome, in two-sample *t*-test with adjustment for the intraclass correlation coefficient (ICC) within a practice site and within a clinician. ^54–56^ Assuming 10% attrition by the 1-week follow-up survey, when quality of the SDM process is measured, we would have 189 patients per arm (378 total). Even with the most conservative ICC at 0.20 and Type I error set at 5%, we would have 80% power for a minimal detectable effect size of 0.38. ^57^ Power will be greater for smaller ICCs. Published studies of the SDM Process (SDMP_4) measure have found effects sizes ranging between 0.30 and 0.60. ^58,59^ Hence, a sample of 378 patients by 1-week follow-up provides sufficient power for our primary outcome. We aim to recruit 25% Black and 15% Hispanic patients to ensure the inclusion of these underserved minority populations.

We also evaluated statistical power and effect sizes for LCS uptake at 6 months, our key secondary outcome, in chi-square tests with adjustment for the ICC within a practice site and a clinician. LCS uptake at 6 months is assessed from EHR data; we will use an intention-to-screen analysis to determine the proportion of participants in each arm who completed screening. Assuming an ICC (clinician and practice) of 0.04 and setting the Type I error at 5%, 210 patients per arm yields 80% power to detect a difference in LCS uptake of 14% in the EUC arm compared to 25.5% in the TELESCOPE arm. We will monitor the ICC during data collection and adjust the sample size (i.e., patients) or recruit additional clinicians if the ICC is higher than anticipated.

Power calculations are not needed for the evaluation of TELESCOPE’s implementation potential (Aim 2) as this is primarily descriptive and qualitative in nature. Our target sample size for the surveys is 131, including primary care clinicians, practice administrators, and patient and nurse navigators. We will conduct approximately 41 interviews with selected individuals from these stakeholders across both study arms. We expect that data saturation will be achieved with this amount of interviews. ^60^

### Data Analysis

To assess impact of the intervention on our primary outcome, we will compare the mean difference in quality of the SDM process (i.e., SDMP_4 score) at the 1-week follow-up (T1) between patients in the TELESCOPE arm and EUC arm. Analyses will include two-sample *t*-test adjusted for a clustering effect (at the level of the patients seen by the same clinician), ^61^ as well as linear mixed model (LMM) adjusted for the study design (clustering at the clinician level). We will compare differences in the average percentage of correct responses (LCS knowledge) and mean decisional conflict scores at 1-week follow-up assessment between the two-arms using *t*-test and LMM, adjusting for the study design. We will compare the difference in percentage of patients who smoke and are referred to tobacco treatment services and received tobacco treatment between the two arms using chi-square tests and LMM with logit link, adjusted for the study design. Finally, we will compare the difference in the percentage of LCS uptake between the two arms using chi-square tests and logistic regression, adjusted for the study design. Furthermore, we will also investigate potential moderators [e.g., race and ethnicity, perceived racial discrimination in healthcare, health literacy, smoking history (current vs former smoker, and pack-year smoking history), family vs. internal medicine, academic practice vs, non-academic] using interaction analysis in the regression models. We will document reasons for dropouts, and perform sensitivity analysis with appropriate missing data modeling techniques to inform interpretation of the results. ^62^

For Aim 2, data from the surveys with clinicians, navigators, and practice administrators will be summarized descriptively, including the median, mean, and range, standard deviations, and frequencies. The interview data will be transcribed and analyzed using Template Analysis^63^, which allows for *a priori* and *in-vivo* coding, to examine the culture of the practices as outlined by PRISM. ^33^ The analysis will also examine barriers and facilitators to implementation. Analysis will be carried out by two independent coders and the inter-rater agreement will be calculated. Disagreements in coding will be resolved either by discussion or adding a third coder.

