### Design

Figure 2 shows an overview of the TELESCOPE study design. We are conducting a cluster RCT with primary care clinicians as the unit of randomization into either (1) the TELESCOPE intervention arm, or (2) an EUC arm. Patients of clinicians in the TELESCOPE arm receive the decision coaching intervention delivered by trained patient navigators (hereafter referred to as ‘decision coaching session’) prior to an upcoming clinic visit with their primary care clinician. Patients of clinicians in the EUC arm have the opportunity to participate in an LCS discussion with their primary care clinician at an upcoming clinic visit. Usual care is enhanced by providing clinicians in both the TELESCOPE and EUC arms with access to a Continuing Medical Education (CME) webinar about LCS and an LCS discussion guide. Patients in the TELESCOPE arm who complete initial screening with negative or benign findings are due for their next screening in 12 months. Half of these participants are randomized to receive a telehealth decision coaching booster session with a patient navigator 1 month before their next annual screening. Table 1 provides a summary of components for the TELESCOPE and EUC arms, which are described in greater detail below.

For the TELESCOPE Trial, a community advisory board of diverse community stakeholders reviews and guides intervention development, recruitment strategies, study procedures, patient-facing materials (e.g., study flyers, informed consent forms, surveys, intervention materials), implementation (e.g., patient recruitment, retention, cultural acceptability), interpretation and dissemination of the results, and identification of next steps.

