### Navigator Training and Fidelity

All patient navigators receive training on decision coaching, which includes: (1) a **1-hour didactic webinar** delivered on Zoom by two subject matter experts (a decision scientist and a clinician) who cover lung cancer epidemiology, what LCS and an LDCT is, LCS guidelines, the importance of SDM for LCS, and the importance of smoking cessation; (2) a **1-hour role-play session** which includes a 30-minute role-play exercise facilitated by a member of the research team in Zoom breakout rooms where patient navigators take turns using the Decision Coaching Manual with another navigator acting as the patient, followed by a 30-minute review of the role-play exercise by the research team; (3) **2 to 3 practice sessions** using the manual with a mock patient, with recordings of the practice sessions reviewed by the research team; and (4) a **1-hour group review session** on Zoom where the research team presents overall feedback from their review of the patient navigators’ practice session recordings. Once a patient navigator can deliver the decision coaching intervention with good fidelity, she/he starts conducting telehealth decision coaching sessions with patients. Patient navigators who need additional training are asked to conduct 1 to 4 additional practice sessions, reviewed by the research team, until they are able to deliver the script with good fidelity.

Intervention fidelity is evaluated by reviewing the first three decision coaching sessions by each navigator, followed by randomly selected 20% of each navigator’s remaining recorded sessions. We use a pilot-tested fidelity checklist to evaluate whether the scientific information presented is accurate and comprehensive, the navigator is capable of conducting the telehealth session over Zoom/Teams, and the navigator demonstrates good active listening skills. Two reviewers independently complete the fidelity checklist for each recording and conflicts in their ratings are resolved through discussion or adding a third reviewer.

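### The planned analysis models clustering by clinician only; if outcomes differ between the navigators who coach the TELESCOPE arm, the interval is too narrow for conclusions beyond those navigators

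*Protocol article*

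**What the plan says.** Clinicians are randomised, and the Design section says that patients of TELESCOPE clinicians "receive the decision coaching intervention delivered by trained patient navigators". Under Description of Intervention these navigators come from the RWJBH Navigation Program. Table 1 records no navigators in the EUC arm.

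The primary outcome is SDMP_4 at 1 week: four items on whether options, pros, cons and preferences were discussed (Patient Surveys). In the TELESCOPE arm the navigator goes through benefits and harms and explores preferences (TELESCOPE Intervention).

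The Data Analysis section specifies a two-sample t-test "adjusted for a clustering effect (at the level of the patients seen by the same clinician" and a linear mixed model with clustering at the clinician level. The secondary comparisons are adjusted for the study design, which that section equates with clinician clustering. The power calculation names practice site and clinician. Neither place has a navigator level.

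The number of navigators, how they are allocated to patients, and a navigator ICC are not given.

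**The concern.** This is a partially nested design: one arm has an extra level of clustering and the other does not. Patients coached by the same navigator share that person's way of conducting the conversation, and the primary outcome is a report on that kind of conversation. A navigator may coach many more patients than the roughly three analysed per clinician, so a clinician intercept does not absorb variation between navigators. With few navigators, that variation does not average out of the TELESCOPE mean.

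The same people help choose a screening location, make the 2-week and 3-month calls and offer tobacco treatment referral, so screening uptake and tobacco outcomes could be affected too.

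At stake is the interval around the primary contrast when it is used to support delivery by other navigators. The Background calls the approach potentially scalable, and the Discussion says the results may inform other integrated health systems.

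**Working it through.** **Inputs from the article (Sample Size and Power Calculation).** "resulting in 420 patients in total (210 patients per arm"; after 10% attrition, "we would have 189 patients per arm (378 total"; "recruit on average 3–4 patients from each of the 120 clinicians"; "Even with the most conservative ICC at 0.20 and Type I error set at 5" per cent. With 60 clinicians per arm, analysed cluster size is m = 189/60 = 3.15. A two-sided test is assumed.

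**The plan's own figure.** The design effect is 1 + (3.15 − 1) × 0.20 = 1.43. In SD units, the variance of the difference in means is V0 = 2 × 1.43/189 = 0.01513, so SE = 0.1230. The effect detectable with 80% power is (1.960 + 0.842) × 0.1230 = 0.345. The stated 0.38 is not reproduced. It is conservative on the stated inputs and is reached only with unstated ones, such as a mean cluster size of about 4.7.

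**Inputs not in the article (assumed).** K navigators with equal caseloads, K = 4 to 30; navigator ICC ρ = 0.01 to 0.05; every TELESCOPE patient coached; navigators regarded as draws from a wider population.

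**Formulas.** The TELESCOPE mean gains variance ρ(1/K − 1/n), with n = 189, so V1 = V0 + ρ(1/K − 1/189). The true SE is R = √(V1/V0) times the one reported. Under a zero population-average effect, the rejection rate at nominal 5% is 2[1 − Φ(1.96/R)].

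**Worked case, K = 6 and ρ = 0.05.** The added variance is 0.05 × (0.16667 − 0.00529) = 0.00807. V1 = 0.02320, R = √(0.02320/0.01513) = 1.24, and the rejection rate is 11.3%, so a nominal 95% interval covers about 89%.

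| K | ρ = 0.01 | ρ = 0.02 | ρ = 0.05 |
|---|---|---|---|
| 4 | 6.9% | 8.8% | 14.5% |
| 6 | 6.2% | 7.5% | 11.3% |
| 10 | 5.7% | 6.5% | 8.7% |
| 20 | 5.3% | 5.7% | 6.7% |
| 30 | 5.2% | 5.4% | 6.1% |

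At ρ = 0 the rate is 5% for any K.

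**Simulation check.** A clinician-clustered test was run on 10,000 trials per setting, for K = 4 to 10 and ρ = 0.01 to 0.05 at clinician ICC 0.20. Rejection was 5.9% to 14.0% with navigators crossed with clinicians and 5.6% to 13.4% with navigators assigned by clinician. With no navigator variation it was 5.2%. Assigning navigators by clinician therefore does not remove the problem.

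**Power.** With navigator variance included and normal quantiles, the detectable effect is 2.80 × √V1. For K = 6 it is 0.380 at ρ = 0.02 and 0.427 at ρ = 0.05; in the latter case power at 0.38 is about 70%. The slack in the stated 0.38 can absorb a small navigator ICC as far as power goes, but it does not correct the interval.

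No corresponding calculation was made for screening uptake.

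**The case against.** **Nothing shows that navigators differ.** They follow a script, start only once they reach good fidelity, and receive continuing feedback and refresher training. This stands, and it makes low ICCs more plausible. Fidelity is checked navigator by navigator, by "reviewing the first three decision coaching sessions by each navigator" and then a 20% sample of the rest. A reader might infer from this, and from the extra practice sessions some navigators may need, that outcomes vary between them. The article shows only that variation is watched for, and gives no estimate.

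**The number of navigators is unknown.** The article says "Our target sample size for the surveys is 131", and a reader might subtract 120 clinicians and infer at most 11 navigators and administrators together. That fails. Surveys go to all clinicians, administrators and navigators; administrators are the medical directors of each site; and there are about 40 sites. Since 120 + 40 = 160 already exceeds 131, the target cannot be a head count of this kind and does not bound the number of navigators. With 20 to 30 navigators the effect is small.

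**The inflation depends on the question asked.** Clinicians are the randomised unit. For the effect as delivered by this trial's own navigators, clinician-clustered inference is valid: simulated rejection was 4.7% to 5.3%. If coaching affected nobody, navigators could not differ in its effect either. This also stands, so the problem belongs to generalisation over navigators and to interval coverage.

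**A condensed article need not list every model.** Its wording on the analyses is not exhaustive, and a navigator sensitivity analysis may exist elsewhere. That lowers the weight of the point. But the article does fix the clustering level for the primary analysis, and that level leaves the navigator out.

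**Conclusion.** The point holds conditionally, as a cheap improvement. If outcomes vary between navigators and the result is meant to apply beyond them, the planned standard error is too small. For navigator ICC 0.01 to 0.05, the rejection rate under a zero population-average effect is about 6% to 15% with 4 to 10 navigators and 5% to 7% with 20 to 30. Interval coverage is correspondingly about 85% to 94% and 93% to 95%. These figures assume clinician ICC 0.20, 189 analysed per arm, equal caseloads and every TELESCOPE patient coached; some uncoached patients would make the effect smaller.

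A reader might go further and infer that the type I error does exceed 5%. The documents do not support that, because they give neither the navigator ICC nor the number of navigators. Nor do they show that each navigator's caseload cuts across clinicians, since allocation is not described; the simulation shows that the conclusion does not depend on it.

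**What to change.** Use the link between session and navigator that per-navigator fidelity sampling already requires, and keep it in the analysis data. Pre-specify a partially nested linear mixed model for SDMP_4: the planned clinician intercept, a navigator random effect for TELESCOPE patients only, each uncoached TELESCOPE patient as a separate unit, and Satterthwaite or Kenward–Roger degrees of freedom. Make it at least a pre-specified sensitivity analysis, with the analogous logistic model for screening uptake.

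Report the number of navigators and the estimated navigator variance. If the conclusion does not hold under this model, limit the claim to the navigators in this trial.

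The change is to analysis wording and needs no new data collection. At the article's status date 134 of 420 patients were enrolled and recruitment was expected to run to May 2026, so on that timetable it could be specified before analysis. The downside is real: with few navigators, a variance from one arm is poorly estimated, degrees of freedom are few, and the interval widens.

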### Randomization

Participating clinicians are randomized 1:1 to either the TELESCOPE or EUC arm, with stratification based on primary practice affiliation at an RWJBH Primary Care Network or a Rutgers academic primary care practice site, and whether the clinician is a family medicine or internal medicine practitioner. Randomization of clinicians is done by the study’s biostatistician (SS) using STATA. After stratification, randomization is constructed within each stratum with random block sizes ranging from 2 to 6. We cannot blind clinicians or patient participants to the intervention. Patient participants are blinded to the study’s specific hypotheses; statisticians and outcome assessors are blinded to the allocation.

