### Patient Surveys

The T0 patient survey assesses knowledge of LCS (using the validated LCS-12 measure^39^), decisional conflict (using the validated Decisional Conflict Scale^40^), cancer fatalism^41^, social norms about LCS^42^, medical mistrust^43^, perceived racial discrimination in healthcare^44,45^, health beliefs about LCS^46^, intentions to undergo LCS, and patients’ sociodemographic characteristics, health literacy, and medical history.

The T1 patient survey assesses the study’s primary outcome, the quality of the SDM process, using the SDM Process (SDMP_4) Scale which includes 4 items assessing whether there was a discussion of options, pros, cons, and preferences for LCS. ^47^ Also assessed at the T1 patient survey are knowledge of LCS, decisional conflict, preparation for decision making (using the validated PrepDM scale^48^), description of the LCS discussion with their clinician, LCS health beliefs, intentions to undergo LCS, and satisfaction with telehealth (for TELESCOPE arm patients) ^49^. In line with PRISM constructs (Table 3), the T1 patient survey also assesses TELESCOPE patients’ acceptability of the intervention (using the Ottawa Acceptability Measure^50^).

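### The main comparisons adjust for clinician clustering only, omitting the two stratification factors and, for knowledge and decisional conflict, the T0 scores; intervals may be wider than they need be

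*Protocol article*

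**What the plan says.** For SDMP_4 at T1, Data Analysis names a two-sample t-test "adjusted for a clustering effect (at the level of the patients seen by the same clinician" and a "linear mixed model (LMM) adjusted for the study design (clustering at the clinician level". It then speaks of adjusting for the study design for knowledge, decisional conflict, tobacco treatment and LCS uptake, without giving the phrase any wider meaning.

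Under Randomization, clinicians are allocated 1:1 in blocks of 2 to 6, "with stratification based on primary practice affiliation at an RWJBH Primary Care Network or a Rutgers academic primary care practice site", and by family versus internal medicine. In Data Analysis these two factors appear only in the list of potential moderators, to be examined by interaction.

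The Sample Size section describes power with "adjustment for the intraclass correlation coefficient (ICC) within a practice site and within a clinician". Data Analysis has no site term.

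Under Patient Surveys, "The T0 patient survey assesses knowledge of LCS (using the validated LCS-12 measure", and decisional conflict is measured in the same survey. Table 2 marks both scales at T0 and T1. Data Analysis compares the "average percentage of correct responses (LCS knowledge) and mean decisional conflict scores at 1-week follow-up assessment between the two-arms" and names no T0 covariate. SDMP_4 differs: "The T1 patient survey assesses the study’s primary outcome, the quality of the SDM process", and Table 2 shows no T0 measurement of it.

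**The concern.** Stratified allocation balances the arms on the stratifying factors, so the arm difference varies less from one possible allocation to another. A model without those factors still counts the between-stratum variance as error. Its standard error is then too large, the interval too wide and the test conservative, provided that the strata are related to the outcome.

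For knowledge and decisional conflict, the T0 score is likely to predict the T1 score. It is also a legitimate covariate, because in the TELESCOPE arm the discussion guide, slides and session link are sent only after the baseline survey is complete. Comparing T1 means alone gives up precision that has already been paid for.

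What is at stake is efficiency, and for the strata also the accuracy of the reported standard error. The risk of a false positive result does not rise.

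**Working it through.** **Inputs from the protocol article.** About 120 clinicians in about 40 sites; 189 patients per arm at T1 (378 in all); ICC 0.20; type I error 5% (taken as two-sided); power 80%; stated detectable effect 0.38 SD. Mean cluster size at T1 is m = 378/120 = 3.15. The article gives no strata variance, no separate site ICC and no T0-T1 correlation, so those are assumed over ranges.

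**The plan's own figures.**
- SDMP_4: design effect = 1 + (3.15 - 1) x 0.20 = 1.43. Detectable effect = (1.960 + 0.842) x sqrt(2 x 1.43/189) = 0.345. With m = 3.5 it is 0.353, and with m = 4 it is 0.365. The stated 0.38 is larger. It needs a design effect of 1.74, which would follow from a coefficient of variation of cluster size of about 0.7, or from a further site ICC of about 0.05. Neither is given, so 0.38 is conservative and not shown to be wrong. At 0.38, power is 87.1%, 85.5% and 83.2% for the three cluster sizes.
- LCS uptake: design effect = 1 + 2.5 x 0.04 = 1.10; 210/1.10 = 190.9 per arm; power for 14% versus 25.5% is 80.8%, in agreement with the stated 80%.

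**Strata, SDMP_4.** With total variance 1, the variance of a clinician mean is V = 0.20 + 0.80/3.15 = 0.454. Suppose that a part s of the 0.20 lies between strata. Adjusting multiplies the variance of the arm difference by (V - s)/V and the interval width by its square root.

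| s | variance ratio | interval width ratio |
|---|---|---|
| 0.01 | 0.978 | 0.989 |
| 0.02 | 0.956 | 0.978 |
| 0.05 | 0.890 | 0.943 |

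A simulation with stratified blocks of 2 to 6 agrees:
- No strata effect: reported SE 0.125 with or without the strata terms, so adjusting neither helps nor harms.
- s = 0.05: without strata terms, reported SE 0.125 against a true SE of 0.116, type I error 0.033. With them, reported SE 0.118, type I error 0.044.
- s = 0.10, beyond the range above: 0.125 against 0.111, type I error 0.025. With strata terms, 0.110 and 0.048.

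The true SE is almost the same with and without the strata terms. The stratified allocation has already gained the precision, and the clinician-only model does not report it.

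**T0 scores, knowledge and decisional conflict only.** Adjusting for a T0 score with correlation r multiplies the variance by 1 - r². This treats the correlation as the same within and between clinicians.

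| r | variance ratio | interval width ratio |
|---|---|---|
| 0.4 | 0.84 | 0.917 |
| 0.5 | 0.75 | 0.866 |
| 0.6 | 0.64 | 0.800 |

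**Practice site.** Sites are not a stratification factor, and 120/40 is about 3 clinicians per site, so the arms cannot be balanced within sites. The generalised least squares variance with random site and clinician effects (40 sites x 3 clinicians, total ICC 0.20), relative to a clinician-only model, is about 0.996, 0.976 and 0.946 for a site share of 0.02, 0.05 and 0.08. That is a gain of about 0.4% to 5%. With site variance, no strata effect and no site term, simulated type I error was 0.044 to 0.057.

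**The case against.** The strongest reply is that nothing promised is lost. The tests stay conservative, and the stated power assumes no gain from covariates. The article is also condensed, and covariate lists commonly belong in an analysis plan. The first part stands: this is an improvement and does not rescue a failing design. The second part carries less weight, because the article does not leave the adjustment open. It defines it in brackets as clinician clustering and then reuses the term. Which of the t-test and the mixed model decides, and whether SDMP_4 should have patient-level covariates, can properly be left to an analysis plan and is not part of this point.

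A reader might infer more than the documents support:
- **That leaving out site invalidates the analysis.** Clinicians are the randomised unit, and a clinician effect absorbs the site variance. What remains is a mismatch in description between the site-and-clinician ICC used for power and the clinician-only analysis.
- **That modelling site yields the 11% variance cut.** That figure requires the whole 0.05 to lie between strata. If it lies between sites, the gain is about 2%.
- **That the T0 gain reaches the primary outcome.** SDMP_4 is measured at T1 only.
- **That enrolling patients after clinicians are randomised makes chance imbalance likelier.** It can allow selection, which is a systematic matter. It does not raise chance imbalance, and stratum terms would not cure selection.

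**Conclusion.** The point holds as one of efficiency. The stated adjustment leaves out the two factors that structured the randomisation and the T0 scores of two secondary outcomes. For SDMP_4 the interval is about 1-6% wider than it need be if the strata carry 1-5% of total variance, and no wider if they are not prognostic. For knowledge and decisional conflict, 16-36% of variance is left unremoved if the T0-T1 correlation is 0.4-0.6, and none if the scores are uncorrelated. All these sizes rest on assumed values. No size is claimed for the binary outcomes. The error is in the conservative direction, so a positive result would not be in doubt because of it.

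**What to change.** In Data Analysis, define adjustment for the study design as clinician random effect plus the two stratification factors (practice affiliation; family versus internal medicine) as fixed effects. Use it in the mixed models and in the logistic models for LCS uptake and tobacco treatment. Add the T0 score as a covariate in the models for knowledge and decisional conflict.

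Optionally, add a random site effect so that the analysis matches the ICC description in the Sample Size section, with only a small gain expected. Fixed effects for some 40 sites are not advisable: in the simulation they raised the reported SE from 0.125 to 0.150 when there was no site variance, and they narrowed the interval only when the site share was very large.

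The cost is wording and a few degrees of freedom: two for the factors, or three if the four cells are fitted, out of about 118 at clinician level (120 - 2). No new data are needed.
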